### Interventions

Participants in the conventional physiotherapy group will receive brief patient education, ultrasound therapy, and stretching and strengthening exercises. The program will be delivered twice weekly for 8 weeks except for the education program which will be provided in two sessions. The stretching exercises will be performed as warm-up and cool-down. Participants in the twice-weekly KBA group will receive two sessions per week of the KBA exercise training for 8 weeks whereas participants in the thrice-weekly KBA will receive three sessions per week of the same exercise training as for the twice-weekly KBA group. Both the two KBA exercise training groups will receive the same intervention program as described for the conventional physiotherapy group prior to receiving the KBA exercise  training. All exercises will be delivered individually under the supervision of the treating physiotherapists. All lower-extremity exercises will be performed bilaterally. The participants will be instructed to perform exercises consistent with their group allocation two times per day at home to encourage self-management. They will be encouraged also to perform a walking exercise of 30 min per day at least 3 to 4 days per week at home. To enhance compliance with the home program, a leaflet with descriptions and pictures of the exercises will be provided to the participants. However, exercises that are more challenging or those requiring the strict supervision of the therapist will be not advised for the home program.

### Brief patient education

Prior to exercise  training, the participants will receive a brief education lasting approximately 15 to 20 min. The program will be delivered by the therapist responsible for exercise  training. It will be provided in a group of 3 to 5 or more participants to save time and effort. The key topics to be addressed include (1) understanding of knee OA, (2) lifestyle and physical activity/exercise, (3) diet and weight control, (4) self-management skills including active coping and pacing as well as correct use of medications (e.g., paracetamol), and (5) ergonomics and joint protection.

### Ultrasound therapy (UST)

The affected knee of the participants will be treated with UST using direct contact technique. A coupling medium (ultrasonic gel) will be used. The treatment parameters to be used include (1) frequency = 1MHz, (2) pulse width = 2.0 W/cm^2^, (3) pulse rest time = 1:1 (continuous mode), and (4) treatment time = 7 min. The UST will precede the stretching and strengthening exercises.

### Stretching and strengthening exercises

Participants will perform 3 lower-extremity stretching and strengthening exercises commonly prescribed for individuals with knee OA as described in previous studies [45, 49]. Progression for the strengthening exercises will be made by increasing the number of sets from 15 s hold to 30 s hold when the 15 s hold is no longer challenging, and the patient is performing an activity with ease and good form. However, the exercise will be discontinued if the patient reports an exacerbation of symptoms. Details of the stretching and strengthening exercises are provided in Table 1.

**Table 1 Tab1:** Stretching and strengthening exercises

**Stretching exercises**			
**Exercise**	**Description**	**Intensity**	
		**Warm-up**	**Cool-down**
1.Hamstring stretch	The patient positioned supine and keeps the knees and hips at 90–90° position. The knee of one leg is then, extended progressively with the foot moving towards the ceiling until it is perpendicular to the floor. Switch sides	15 s × 6 sets	15 s × 6 sets
2.Quadriceps stretch	Patient positioned in side-lying and grasps the forefoot behind. The forefoot or ankle is pulled to a rear end. Switch sides	15 s × 6 sets	15 s × 6 sets
3.Calf stretch	The patient sits with the legs straight out in front. One leg is bent and a towel is placed around the ball of the opposite foot. While keeping the knee straight, pull the foot towards the body with the towel. Switch sides	15 s × 6 sets	15 s × 6 sets
**Strengthening exercises**			
**Exercise**	**Description**	**Intensity**	
1.Static quadriceps isometrics	The patient stands with one leg straight and the knee of the opposite leg flexed, and the foot flat on the ground. A rolled towel or a cushion is placed underneath the straight leg’s knee. The straight knee is then pressed on the towel and the position is held. Switch sides	15–30 s × 6 sets	
2**.**Seated knee extension	The patient sits on a chair with one foot flat on the floor and straightens the opposite foot. Switch sides	15–30 s × 6 sets	
3. Lying leg curl	The patient lies prone and squeezes the inner thigh to keep the legs close next to each other. The legs are then bent as far as possible by bringing the heels in towards the buttocks	15–30 s × 6 sets	

### Kinesthesia, balance and agility exercises

The exercise regimen of KBA will be done by performing a series of walking-based agility and balance exercises. The exercise protocol was adapted from previous studies [42, 44, 45] but with slight modifications regarding the training intensity and addition of visual manipulation for some selected walking-based agility exercises. The participants will perform agility exercises before proceeding to static and dynamic balance exercises. For the agility exercises, participants will begin each exercise with a walking pace of approximately 15 steps and progress to a maximum of approximately 75 steps [44, 45]. For balance training, participants will start with exercises while standing on a hard surface or floor and then proceed to exercises while standing on a form surface (Balance Soft Mat, BigMall, Nigeria). The form provides a more difficult task compared to the hard floor. Static balance exercises will be performed before progressing to dynamic balance exercises. For example, static balance will begin with a one-leg stand on a hard floor before progressing to a one-leg stand on the trainer foam [45]. The dynamic balance exercises will be progressed in the same manner but will require perturbations in different directions to be provided by the physiotherapist. The progression of each balance exercise to the next will be based on the participant’s ability by starting with the less stressful and challenging ones and increasing the number of repetitions. Participants will perform at least 3 sets of each exercise, and there will be 10 to 20 s rest between each exercise. All exercises will be progressed according to the individual’s tolerance and abilities within the structure of the program. If an exercise proved very difficult, the duration of the exercise will be adjusted based on the patient’s ability but no activity will be eliminated. However, the exercise will be discontinued if the patient reports an exacerbation of symptoms. The details of the KBA exercises are presented in Table 2.

**Table 2 Tab2:** Kinesthesia, balance and agility exercises

Progression	Exercise	Treatment intensity
Weeks 1–3	Side stepping	15–75 steps × 3 sets
	Semi-tandem walk	15–75 steps × 3 sets
	Tandem walk	15–75 steps × 3 sets
	Crossbody leg swings	15–75 steps × 3 sets
	Crossover forward walk	15–75 steps × 3 sets
	Crossover backward walk	15–75 steps × 3 sets
Weeks 4–6	Toe walk	10–30 s × 3 sets
	Heel walk	10–30 s × 3 sets
	Multiple changes in direction drill (forward, backward, sideways as directed by the therapist)	10–20 s × 3 sets
	One-leg stand on a hard surface with eyes open	10–30 s × 3 sets
	One-leg stand on a hard surface with eyes closed	10–30 s× 3 sets
	Double-leg stand (eyes open) on a hard surface with perturbations	10–30 s × 3 sets
	Double-leg stand (eyes closed) on a hard surface with perturbations	10–30 s × 3 sets
Weeks 7–8	Crossover forward walk with eyes closed	15–75 steps × 3 sets
	Crossover backward walk with eyes closed	15–75 steps × 3 sets
	One-leg stand on a foam surface with eyes open	10–30 s × 3 sets
	One-leg stand on a foam surface with eyes closed	10–30 s × 3 sets
	Double-leg stand (eyes open) on a foam surface with perturbations	10–30 s × 3 sets
	Double-leg stand (eyes closed) on a foam surface with perturbations	10–30 s × 3 sets

### Outcome assessments and follow-ups

The primary outcome will be physical function whereas the secondary outcomes will be pain intensity, knee stability, proprioception, and quality of life. Similar to previous trials on knee OA, if only one knee of the patient is affected, the evaluation of the outcomes will be done for this knee. If the patient has bilateral affectation of which only one meets the ACR criterion [48], only this knee will be evaluated. However, if the patient is having bilateral affectation according to the ACR criterion, the more painful knee will be selected for outcome evaluation.

All outcomes will be assessed pre-intervention, immediately post-intervention and at 3 months, 4 months, and 6 months post-randomization. Participants missing their regular appointments will be given makeup appointments until they reach the required sessions for each group. This will be done by contacting them through phone calls. All participants will be advised to refrain from other interventions during the trial except for those taking medications as prescribed by their physician and this information will be collected.

### Physical function

The physical function of the participants will be assessed with the Hausa version of the Ibadan Knee and Hip Osteoarthritis Outcome Measure (IKHOAM) [50]. It is a 33-item instrument with 3 domains consisting of activity limitations, participation restrictions, and physical performance tests to assess physical function. Each item is rated on a Likert scale that ranges from 0 to 5. The measure is a Nigerian culture and environment-friendly clinical instrument developed for individuals with knee OA [51]. To obtain the patient’s percentage perceived level of physical function, the participant’s scores obtained are divided by the total possible score (232) and then multiplied by 100. Lower scores indicate a lower level of physical functioning [51]. The Hausa IKHOAM has been shown to have adequate internal consistency (0.64–0.95) and construct validity [50].

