### Sample size estimation

Based on the results of our pilot study (unpublished data), using the effect size of 0.185 for between-group difference in the primary outcome (physical function measured by IKHOAM), a priori sample size was calculated assuming a statistical power of 90%, an alpha of 5% (two-tailed), and an effect size of 0.47. The calculations suggested a sample size of 102 would be needed. However, while anticipating a 20% attrition rate (*n* = 20), a total sample size of 120 will be needed with 40 participants per group. The calculations were performed with the G-power 3.1.9.2 software (University of Dusseldorf, Dusseldorf, Germany) [67].

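### The primary-outcome scoring rule contradicts itself: 33 items rated 0 to 5 can total at most 165, yet the percentage is taken out of 232

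*Protocol article*

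**What the plan says.** Protocol article, Outcome assessments and follow-ups, fixes the hierarchy of outcomes: "The primary outcome will be physical function whereas the secondary outcomes will be pain intensity, knee stability, proprioception, and quality of life".

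The Physical function section then defines the measure. On length and structure: "It is a 33-item instrument with 3 domains consisting of activity limitations, participation restrictions, and physical performance tests to assess physical function". On item scoring: "Each item is rated on a Likert scale that ranges from 0 to 5". On conversion to a percentage, the participant's score is "divided by the total possible score (232) and then multiplied by 100". On direction: "Lower scores indicate a lower level of physical functioning", so a higher percentage means better function.

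The section mentions no weighting of items, no item rated more than once and no item with a range other than 0 to 5. The Quality of life section adds that participants who prefer English may complete the English form of the instrument, so the rule has to serve two language versions.

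**The concern.** A percentage score needs a denominator equal to the highest sum that the items can produce. Here the denominator exceeds that sum by 232 − 165 = 67 points, which is too much for a rounding slip. At least one of the three figures in the scoring rule is therefore wrong or incomplete as written.

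The Statistical analysis section summarises continuous variables by means and SDs, so readers will take the size of the primary effect from this percentage scale. If the denominator is too large, those values are too small, and they cannot be set beside IKHOAM percentages from studies that used the correct maximum. If the denominator is right, a reader working from the published description cannot reproduce the score.

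**Working it through.** **Inputs** (all from Protocol article, Physical function): 33 items; maximum per item 5; stated total 232.

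**1. Try to reproduce 232.** Maximum sum = items × maximum per item = 33 × 5 = 165. The stated total is not reproduced.

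**2. Look for a simple slip that would give 232.**

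| Variant | Result |
|---|---|
| Maximum of 6 per item | 33 × 6 = 198 |
| Maximum of 7 per item | 33 × 7 = 231 |
| Average maximum needed for 33 items | 232/33 = 7.03 |
| Number of ratings needed at maximum 5 | 232/5 = 46.4, not a whole number |
| Some items rated once and *b* of the 33 rated twice, all 0 to 5 | 165 + 5*b* = 232, so *b* = 67/5 = 13.4, no solution |

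No whole number of ratings with a maximum of 5 gives 232. A mixture of maxima can. For example, 44 ratings with maximum 5 and 3 with maximum 4 give 220 + 12 = 232, but that is 47 ratings, and the article describes nothing of the kind.

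**3. Size if 33 items and 0 to 5 are right, each item rated once.**

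- Highest attainable percentage: 165/232 = 0.711, or 71.1%.
- Shrinkage of every mean, SD and difference in percentage points: 1 − 165/232 = 28.9%.
- A difference of 10 points on a true 0–100 scale is reported as 10 × 0.711 = 7.1.
- In raw terms, 10 score points become 10/232 = 4.31 percentage points instead of 10/165 = 6.06.

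**4. Size if 232 is right.** The item count or item range is misdescribed, the scale reaches 100%, and the shrinkage is 0%.

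**5. Effect on inference.** Changing the denominator multiplies every score by the same constant. Means, differences and SDs all change by that factor, so it cancels in F ratios and standardised effects, and ranks do not move. As a check on simulated scores (34 per arm, means 90, 100 and 105, SD 20), a one-way F test gave F = 4.657 and p = 0.0117 with either denominator.

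**6. Effect on sample size.** The calculation starts from a pilot value, "using the effect size of 0.185 for between-group difference in the primary outcome (physical function measured by IKHOAM", and then uses 0.47. Reading 0.185 as eta-squared gives f = √(0.185/0.815) = 0.476, close to the stated 0.47, so both figures look unit-free. No percentage-point difference enters the calculation.

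**The case against.** The strongest reply is that 232 may be the instrument's true maximum and that the article has only simplified its description of the items. One of the three domains consists of physical performance tests, which could well be scored differently from questionnaire items. A total that is not a multiple of 5 fits a condensed item description at least as well as a wrong denominator. This stands. A reader might infer that a fully functional participant will score 71% and that the trial will understate its effect by 29%, but the document supports those figures only on condition that the item count, the item range and single rating are all correct. Settling the question needs the instrument's own scoring material, which is not in the document.

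It is also fair to say that no planned test is affected. The mixed ANOVA, the Friedman and Kruskal–Wallis tests, the Bonferroni comparisons and standardised effect sizes are unchanged by a constant factor, and the article applies no percentage-point threshold to the IKHOAM. This stands too, and it limits the harm to reported magnitude and comparability.

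Two further inferences are tempting and should not be drawn.

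- A fixed denominator might suggest that unanswered items or tests not performed count as zero. The article does not say so. Its Statistical analysis section plans multiple imputation by chained equations, its Data management section has assessors check for missing values, and item-level rules are commonly left to a fuller document. For the same reason, there is no basis here for replacing the stated rule with a prorated one.
- The four hospitals might be thought likely to resolve the conflict differently. The article states a single denominator, trains all the physiotherapists in the same way and has one independent statistician run all analyses.

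None of this removes the contradiction itself, which lies in consecutive, intact sentences about the primary outcome.

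**Conclusion.** The contradiction is certain: 33 items, a 0 to 5 range and a total of 232 cannot all hold. Which figure is at fault is not known from the document. The consequence therefore lies between two readings:

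- **Item count and range right, each item rated once:** ceiling 71.1%, and all percentage-point means, SDs and differences 28.9% too small.
- **Total of 232 right:** no shrinkage, but the item count or range is misdescribed and the score cannot be reproduced from the article.

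Under both readings p-values, standardised effects and the sample size stand, provided that the same denominator is used for everyone, as the article states. This is a correction worth making before analysis because it concerns the primary outcome. It is not a threat to the validity of the comparison.

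**What to change.** Before analysis:

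1. Check the item count, the range of each item and the maximum of each domain against the instrument's scoring sheet.
2. Correct whichever of the three figures is wrong. Do not assume that it is 232.
3. State any item that has another range or is rated more than once, so that the stated maximum follows from the description.
4. Use the one confirmed denominator for both the Hausa and the English forms.

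The cost is a corrected sentence or two in the Physical function section and, if the denominator changes, one line of scoring code. No new data are needed, and scores already computed can be rescaled by a constant.

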### Pain intensity

The Visual Analogue Scale for pain (VAS-pain) will be used to assess participants’ pain severity. It represents the intensity dimension by a 100 mm bidirectional plain line with anchor points of “no pain” (0 mm) and “worst possible pain” (100 mm) located at either end of the line [52]. Participants will be asked to rate their current level of pain by marking anywhere along the 100mm line that best indicates thier knee pain. The VAS-pain has been commonly used to evaluate pain intensity in osteoarthritic knee pain. The Hausa version of the VAS-pain has adequate alternate forms reliability (r = 0.93) [53] and construct validity [54] and will be used in this study.

### Knee stability

Participants’ subjective reports of knee stability will be measured with the Knee Outcome Survey-Activities of Daily Living Scale (KOS-ADLS). It is a 14-item questionnaire that assesses symptom-related and specific functional limitations [55]. Six items assess knee symptoms (pain, stiffness, swelling, instability, weakness, and limping), and eight items assess functional limitations (walking, stairs ascent/descent, standing, kneeling, squatting, sitting, and rising from a sitting position) experienced in the last 1 to 2 days during the performance of daily activities. Each item is scored on a 6-point Likert scale (0–5 points) [56]. The score is transformed to a 0–100 point scale with the highest score indicating the absence of symptoms and functional limitations [55]. For the purpose of this study, only the item pertaining to knee instability symptoms will be evaluated. The KOS-ADLS has been shown to have excellent internal consistency (0.92–0.93), test-retest reliability (intraclass correlation coefficient [ICC] = 0.97), and adequate construct validity [55].

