### Quality of life

The quality of life of the participants will be measured using the mini Osteoarthritis Knee and Hip Quality of Life Questionnaire (OAKHQOL) [63]. It is a 20-item questionnaire derived from the original 40-item questionnaire developed by Rat et al. [64]. The questionnaire consists of five dimensions subscales: physical activities, mental health, pain, social support, and social functioning; and three independent items addressing sexual life, professional life, and fear of being dependent. Each item is measured on a numerical rating scale from 0 to 10 and the mean item score becomes the corresponding dimension score [63]. The mini OAKHQOL has been shown to have adequate internal consistency (0.78–0.95), test-retest reliability (ICC = 0.66–0.89), and factorial validity in subjects with knee and hip OA [65].

As no Hausa versions of the KOS-ADLS and OAKHQOL are available for use, these questionnaires will be translated from English into Hausa language using guidelines for the process of cross-cultural adaptation of self-report measures [66]. This is to ensure that reliable data is collected and participants who are unable to complete English measures are not excluded in the trial [54]. However, English versions of IKHOAM, VAS-pain, KOS-ADLS, and OAKHQOL will be applied to those willing to respond in English.

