### Statistical analysis

An independent statistician who will be blinded to the study procedures will conduct all statistical analyses. The normality test of the data will be verified with the Shapiro–Wilk test and visual inspection of distribution plots. To account for potential missing data in datasets, per-protocol (PP) and intention-to-treat (ITT) approaches will be considered for the data analysis. For the PP approach, only participants who completed all treatment sessions will be included in the analysis. For the ITT approach, multivariate imputation by chained equations will be employed [68]. Descriptive statistics of mean and standard deviation will be used to summarize all continuous variables while frequency and percentages will be used to summarize all categorical variables. Mixed between-within subject ANOVA will be used to assess interaction effect (group x time), main effects for time, and between-subjects effect if the data is normally distributed. However, Friedman’s ANOVA and Kruskal–Wallis test will be used to analyze within-group change and between-group difference, respectively, if the data is not normally distributed. Post hoc analysis using Bonferroni correction will be conducted for any significant between-group difference observed. Effect size will be also computed to determine the magnitude of change in outcomes. All data will be analyzed using SPSS version 23 (IBM Co., Armonk, NY, USA) at an alpha level of 0.05.

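### Knee stability is a single six-level item that the normality rule will in practice send to rank tests with no baseline adjustment and no group-by-time test

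*Protocol article*

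**What the plan says.** The Knee stability section introduces the KOS-ADLS: "It is a 14-item questionnaire that assesses symptom-related and specific functional limitations". On scoring it says "Each item is scored on a 6-point Likert scale (0–5 points") and, for the scale, "The score is transformed to a 0–100 point scale with the highest score indicating the absence of symptoms and functional limitations". It then restricts the outcome: "only the item pertaining to knee instability symptoms will be evaluated". The next sentence gives reliability for the instrument: "The KOS-ADLS has been shown to have excellent internal consistency (0.92–0.93), test-retest reliability (intraclass correlation coefficient [ICC] = 0.97").

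The Quality of life section adds "As no Hausa versions of the KOS-ADLS and OAKHQOL are available for use", so a translation will be made for the trial.

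The Statistical analysis section applies one rule to all outcomes. Normality is checked by Shapiro–Wilk and by looking at plots. If the data are normal, a mixed ANOVA tests group, time and their interaction. If not, Friedman's ANOVA and the Kruskal–Wallis test "will be used to analyze within-group change and between-group difference, respectively, if the data is not normally distributed". No baseline covariate is named in either branch. The section does not say whether Kruskal–Wallis is run on post scores or on change.

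The Baseline assessment section lists knee stability among the measures taken before randomization. The outcome section schedules five assessments, one before the intervention and four after it.

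**The concern.** The form of this outcome largely settles which branch it takes. One item scored 0–5 has six possible values, and rescaling it to 0–100 would not add any. Data this coarse are rejected by a normality test at modest sample sizes even when the underlying trait is normal. Knee stability should therefore be expected to go to Friedman and Kruskal–Wallis.

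Two things are then lost. The group-by-time test exists only in the ANOVA branch. Friedman tests describe change inside one arm and do not compare arms. In addition, no adjustment is made for a baseline value that the trial collects anyway. At stake is power on a pre-specified secondary outcome. The primary outcome and the sample size are not affected.

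A smaller matter is that the reliability figures sit directly after the sentence that restricts the outcome to one item. Internal consistency is not defined for one item, and the test–retest ICC of a 14-item score is not that of one of its items.

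**Working it through.** **Inputs from the protocol article.** One item with six levels; baseline value collected; 40 randomized per arm; 102 patients before attrition, so 102/3 = 34 per arm; two-sided alpha 0.05. The article states no power for knee stability, so there is no figure of its own to reproduce.

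**Assumptions not in the article.** The item is a normal latent variable cut into six categories. Category shares are symmetric, skewed (0.03, 0.07, 0.15, 0.25, 0.30, 0.20) or near the ceiling (0.02, 0.03, 0.08, 0.17, 0.30, 0.40). Latent shifts in the three arms are 0, 0.3 and 0.6 SD. Latent baseline-to-follow-up correlation is 0 to 0.7. One follow-up visit is simulated, with 2,000 trials per scenario.

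**Step 1: which branch.** Shapiro–Wilk rejected in essentially 100% of simulated trials, both pooled (102–120 patients) and in at least one arm of 34–40, even for the symmetric item. In single samples of 32 (40 × 0.8, after 20% attrition) it rejected in roughly 78–100%, depending on the cut points.

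**Step 2: what theory predicts.** For a continuous outcome with correlation ρ, the variance relative to an unadjusted post score is:
- change score: 2(1 − ρ) = 1.40, 1.00, 0.60 at ρ = 0.3, 0.5, 0.7
- baseline-adjusted: 1 − ρ² = 0.91, 0.75, 0.51 at the same values

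Adjustment is never worse than either alternative. It helps little over post scores at 0.3.

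**Step 3: simulated power.** KW is Kruskal–Wallis. PO is the 2-df likelihood-ratio test of arm in a proportional-odds model.

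| Item, per arm | ρ | KW post | KW change | PO unadjusted | PO + baseline | Gain over KW post | Gain over KW change |
|---|---|---|---|---|---|---|---|
| Skewed, 34 | 0.3 | 0.508 | 0.321 | 0.523 | 0.558 | 0.050 | 0.237 |
| Skewed, 34 | 0.5 | 0.515 | 0.436 | 0.536 | 0.644 | 0.129 | 0.208 |
| Skewed, 34 | 0.7 | 0.516 | 0.598 | 0.540 | 0.767 | 0.251 | 0.169 |
| Skewed, 40 | 0.3 | 0.581 | 0.377 | 0.595 | 0.634 | 0.053 | 0.257 |
| Skewed, 40 | 0.5 | 0.582 | 0.484 | 0.596 | 0.703 | 0.121 | 0.219 |
| Skewed, 40 | 0.7 | 0.593 | 0.693 | 0.607 | 0.856 | 0.263 | 0.163 |
| Ceiling, 40 | 0.3 | 0.548 | 0.294 | 0.560 | 0.590 | 0.042 | 0.296 |
| Ceiling, 40 | 0.5 | 0.536 | 0.395 | 0.550 | 0.644 | 0.108 | 0.249 |
| Ceiling, 40 | 0.7 | 0.547 | 0.539 | 0.561 | 0.772 | 0.225 | 0.233 |

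Across the symmetric and ceiling items at 40 per arm, the gain over KW on post scores is about 0.02 at ρ = 0, 0.04–0.05 at 0.3, 0.11–0.13 at 0.5 and 0.23–0.28 at 0.7. The Monte Carlo standard error of one power estimate is about √(0.5 × 0.5/2,000) = 0.011.

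**Step 4: where the gain comes from.** The unadjusted proportional-odds test exceeds KW by only 0.01–0.02. At 34 per arm and ρ = 0.5, adding baseline accounts for 0.644 − 0.536 = 0.108 of the total 0.129. Linear models show the same: ANOVA 0.511 against ANCOVA 0.618.

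**Step 5: a rank alternative.** A separate run of 2,000 trials at 34 per arm, with the same shifts, used a baseline-adjusted rank analysis. At ρ = 0.3, 0.5 and 0.7 its power was 0.58, 0.62 and 0.79. KW gave 0.55, 0.52 and 0.53 on post scores, and 0.37, 0.46 and 0.65 on change. The gains over post scores are 0.03, 0.10 and 0.26.

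**Step 6: cost.** With no true effect, the adjusted proportional-odds test rejected in 0.050–0.066 of trials and KW in 0.042–0.054. With unequal spread between arms and no latent shift, the rates were 0.069 and 0.052–0.060. The rank analysis stayed at 0.046–0.059, so the gain is not produced by an inflated test. Sparse cells are likely: 34 × 0.03 ≈ 1 patient per arm in the lowest skewed category.

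**The case against.** The strongest reply is that the rule is general and conditional. It never names knee stability, it includes a look at plots, and an unseen analysis plan may set outcome-specific models. Kruskal–Wallis is also a valid test for an ordinal score.

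Part of this stands. The routing is an inference, though a strong one, and to say that the plan forces the rank tests would go too far. The reply does not remove the point, because the article has fixed a rule rather than left one open, and that rule fits this outcome poorly. If the plots led the analyst to ANOVA instead, a six-level item would be treated as interval data and still not be adjusted for baseline.

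A reader might infer several stronger things that the article does not support:
- *That the baseline value goes unused.* Friedman would naturally include it as a repeated measure, and Kruskal–Wallis may be run on change, which also partly answers the group-by-time question. What is missing is covariate adjustment.
- *That a better analysis is free.* Step 6 shows a small cost.
- *That the ordinal model brings the power.* Baseline adjustment brings nearly all of it.
- *That the reliability sentence is false.* It describes the KOS-ADLS as an instrument. The fair criticism is that its figures do not carry over to the one item used.

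The simulations cover one follow-up visit. They do not measure the power of a longitudinal ordinal model with an arm-by-visit term.

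**Conclusion.** The point holds as a conditional gain in efficiency on a secondary outcome. Knee stability will almost certainly reach the rank-test branch, which has no baseline covariate and no group-by-time test.

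Against Kruskal–Wallis on post scores, adjustment is worth about 3–5 power points at a correlation of 0.3, 11–13 at 0.5 (10 for the rank analysis) and 23–28 at 0.7. Against Kruskal–Wallis on change, the gain at 0.7 falls to about 14–17 points for the skewed item and the rank analysis, and stays near 23 for the ceiling item. At 0.3 and 0.5 it is larger than against post scores.

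All of this rests on assumed shifts, category shares and correlations, none of which the article gives. If the true correlation is about 0.3 or lower, the benefit over post scores is slight. The reliability issue is a wording correction and changes no result.

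**What to change.** In Statistical analysis, exempt knee stability from the normality-gated choice and pre-specify one comparison of arms adjusted for the baseline item. A suitable choice is a proportional-odds model over the follow-up visits with arm, visit, arm × visit and the baseline item, allowing for repeated measures on the same patient. State in advance that a baseline-adjusted rank analysis will be used if categories are too sparse.

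In Knee stability, name the outcome *KOS-ADLS instability item (0–5)*. State that the internal consistency of 0.92–0.93 and the ICC of 0.97 belong to the 14-item scale, not to this item.

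The cost is wording and some analysis work, with no new data and no change to sample size. The proportional-odds assumption must be checked, effects would be reported as odds ratios, and the likelihood-ratio test may run slightly above its nominal level. The change should be recorded before allocation is revealed to the analyst.
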